### Study design

The current trial is a 6-month, randomized, open-label, non-blinded, prospective, single-center study of efficacy and safety comparing concentration-controlled everolimus and MSCs to everolimus with standard tacrolimus. The protocol has been authorized by the Dutch Government (CCMO) and by the Committee Medical Ethics of the LUMC (Leiden University Medical Center).

In total, 70 de novo renal recipients, 18–75 years of age will be recruited from the transplant clinics of the LUMC and enrolled into the study if they meet the eligibility criteria.

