**Methods/design:**

70 renal allograft recipients, 18–75 years old, will be included in this Phase II, open label, randomized, non-blinded, prospective, single centre clinical study. Patients in the MSC treated group will receive two doses of autologous bone marrow derived MSCs IV (target 1,5x10^6^, Range 1-2x10^6^ million MSCs per/kg body weight), 7 days apart, 6 and 7 weeks transplantation in combination with everolimus and prednisolone. At the time of the second MSC infusion tacrolimus will be reduced to 50% and completely withdrawn 1 week later. Patients in the control group will receive everolimus, prednisolone and standard dose tacrolimus. The primary end point is to compare fibrosis by quantitative Sirius Red scoring of MSC treated and untreated groups at 6 months compared to 4 weeks post-transplant. Secondary end points include: composite end point efficacy failure (Biopsy Proven Acute Rejection, graft loss or death); renal function and proteinuria; opportunistic infections; immune monitoring and “subclinical” cardiovascular disease groups by assessing echocardiography in the different treatment groups.

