## Methods and design

### Objectives and endpoints

The primary end point of the current study is the level of fibrosis, as determined by quantitative Sirius Red (SR) scoring of biopsies of MSC treated and untreated groups at 6 months compared to 4 weeks post transplantation. Other endpoints include: composite endpoint efficacy failure (Biopsy Proven Acute Rejection (BPAR), graft loss) at 6 months; renal function measured by eGFR (MDRD formula and iohexol clearance) and proteinuria at 6 months; cytomegalovirus (CMV), BK infection (viremia, disease and -syndrome) and other opportunistic infections; adverse events; the presence of DSA and other phenotypical and functional aspects of the donor specific immune response; to compare the progression of “subclinical” cardiovascular disease in the different treatment groups by assessing echocardiography.

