### Fibrosis scoring by renal biopsy

A standard renal protocol biopsy is performed prior to the transplantation and at 6 months after transplantation. At 4 weeks after transplantation a study biopsy is taken to assess the renal histology before MSC infusion. Biopsies are scored according to the Banff criteria and processed for immunohistochemistry (HE staining; staining for CD3, CD4, CD68, FOXp3, C4d and CD20). In addition, the amount of cortical collagen (SR-positive area) will be measured and finally expressed as the percentage of the total analyzed cortical surface. Moreover, changes in mRNA expression of pro- and anti-fibrotic genes (including FGFb and fibronectin) in renal biopsies taken before and after MSC infusion through real-time quantitative PCR will be performed.

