
One of the important issues in the MSC-based clinical trials is defining endpoints, as this is the measure of trial failure or success. However, this is very challenging in patients after solid organ transplantation, where an increased risk for infections and malignancies already exists and where there is a lack of validated surrogate markers of disease. The therapeutic aim of MSC-based trials in renal transplant recipients is to induce immune suppression and repair of damaged tissue but without the risk of inducing tumours, infections, or unwanted tissue development, and obviously without increasing allograft rejection rates and diminishing allograft survival. Therefore both safety and efficacy measures have to be addressed. Efficacy markers in our trial include laboratory studies to determine possible development of donor-specific immunosuppression and histopathologic evaluation of renal tissue to evaluate both inflammation and fibrosis before and after the treatment. The primary endpoint in our study is the comparison of fibrosis by quantitative SR scoring of MSC treated and untreated groups at 6 months compared to 4 weeks post-transplant. Once established, interstitial fibrosis and arteriolar hyalinosis lead to progressive glomerulosclerosis over the subsequent years. In earlier studies nephrotoxicity, implicated in late ongoing injury, has been shown to be almost universal at 10 years, even in grafts with excellent early histologic findings. By 10 years, severe chronic allograft nephropathy was present in 58.4% of patients, with sclerosis in 37.3% of glomeruli. Tubulointerstitial and glomerular damage, once established, was irreversible, resulting in declining renal function and graft failure [38,53-56]. Functional studies underestimate the extent of allograft disease as supported by longitudinal studies of protocol renal biopsies showing histologic features of IF/TA in well-functioning grafts [38,39,56-58]. Therefore, early histologic detection of IF/TA has been suggested to be helpful in predicting the risk for subsequent loss of function and time to graft failure and to estimate the efficacy of therapeutic measures. Semiquantitative grading systems such as Banff scores have a wide inter-observer variation that makes comparison across centers inaccurate. In contrast, computerized image analysis of fractional interstitial fibrosis of SR-stained biopsies has been shown to be a valid and reproducible method to measure the degree of fibrosis [40,41,43,59,60]. SR dye is specific for collagen types I and III, which represent respectively 80 and 20% of total collagen synthesized by fibroblasts and thereby important components of renal matrix. Quantification of renal interstitial volume assessed by SR nonpolarized technology has been validated and correlated significantly with GFR as measured by iothalamate clearance in cases of established chronic allograft nephropathy [59]. In addition, in 2011 morphometric and visual evaluation of fibrosis by various techniques was compared and Collagen III, SR unpolarized had strongest correlations, greatest dynamic range and the best correlation with estimated GFR [61].

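### The trial is labelled non-blinded with no exception for biopsy readers, and no masked reading is described for the slide-based primary endpoint or for BPAR

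*Protocol article*

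**What the plan says.** The abstract calls the trial a "Phase II, open label, randomized, non-blinded, prospective, single centre clinical study", and the Study design section calls it a "6-month, randomized, open-label, non-blinded, prospective, single-center study of efficacy and safety". Neither place limits the label to patients and treating staff.

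Under Objectives and endpoints, the primary endpoint is fibrosis "as determined by quantitative Sirius Red (SR) scoring of biopsies of MSC treated and untreated groups at 6 months", compared with 4 weeks. The secondary list includes the "composite endpoint efficacy failure (Biopsy Proven Acute Rejection (BPAR), graft loss) at 6 months". The section Fibrosis scoring by renal biopsy says that biopsies are Banff-scored and that "the amount of cortical collagen (SR-positive area) will be measured and finally expressed as the percentage of the total analyzed cortical surface". It mentions neither coded slides nor what the reader knows.

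The Discussion gives the reason for choosing Sirius Red: "Semiquantitative grading systems such as Banff scores have a wide inter-observer variation", which in that sentence is a problem for comparing centres, whereas "computerized image analysis of fractional interstitial fibrosis of SR-stained biopsies has been shown to be a valid and reproducible method".

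The only other reference to blinding is in the section on the data safety monitoring committee, where serious adverse events are reviewed unblinded. The same section ends the study if the rejection rate reaches 30%.

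**The concern.** Treatment cannot readily be masked here, because one arm has bone marrow harvest, cell infusions and tacrolimus withdrawal. Slides can be masked. An unqualified non-blinded label, with no masking in the scoring section, permits a reader who knows the arm to score both the primary endpoint and rejection.

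The two endpoints are not equally exposed. Banff grading is a visual judgement. It decides BPAR, which enters the secondary composite and is the natural source of the rejection rate behind the 30% termination rule. Sirius Red is a measured area, so the reader has less room. Its denominator is, however, the cortical surface that was analysed, and if a person selects that surface, some discretion remains. The article does not describe this step, so it is an assumption.

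A reading error that leans towards one arm is a bias. It adds directly to the estimated difference, and enrolling more patients does not shrink it.

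**Working it through.** **1. Inputs, all from Sample size calculation.** Control mean 18%, MSC mean 14%, so the target difference is 4 points; common SD 5; two-sided alpha 0.05; two-group t-test; 25 evaluable per group for 80% power; 70 enrolled with 70% expected to have valid measurements.

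**2. The plan's own figure reproduces.**
- n per group = 2 × (1.960 + 0.842)² × 5² / 4² = 2 × 7.85 × 25 / 16 = 24.5, rounded up to 25.
- Power at 25 per group is 0.807 by the normal approximation and 0.791 by the exact noncentral t.
- Expected evaluable patients: 70 × 0.70 = 49, or 24 against 25.

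**3. Effect of an arm-directed reading shift.** The documents give no size for such a shift, so the values of b below are assumptions, shown as a range. Suppose there is no true effect and reading moves the arm difference by b points.
- Standard error of the difference = 5 × √(2/25) = 1.414.
- Noncentrality = b / 1.414, with 48 degrees of freedom.
- False-positive rate = probability that the noncentral t falls outside the two-sided 5% limits.

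| Assumed shift b (points) | Share of 4-point target | Noncentrality | False-positive rate, 25 v 25 | 24 v 25 |
|---|---|---|---|---|
| 0 | 0 | 0 | 5.0% | 5.0% |
| 0.5 | 1/8 | 0.35 | 6.4% | 6.4% |
| 1 | 1/4 | 0.71 | 10.7% | 10.5% |
| 1.5 | 3/8 | 1.06 | 18.0% | 17.7% |
| 2 | 1/2 | 1.41 | 28.3% | 27.8% |

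The SD is the one the plan assumes for measured fibrosis. If the analysis uses change from 4 weeks, its SD may differ and these rates would move.

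**4. More patients do not help.** With 100 per arm the standard error is 5 × √(2/100) = 0.707. The same 1-point shift then has noncentrality 1.41 and gives about 29% false positives.

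**5. Which knowledge matters.** Both arms are biopsied at 4 weeks and 6 months. A shift tied only to time point affects both arms alike and cancels on average in the between-arm comparison. The coding therefore has to hide the arm.

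**6. BPAR.** The documents give neither an expected rejection rate per arm nor a misreading rate, so no comparable figure is offered for BPAR.

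**The case against.** The strongest reply is that the article is silent rather than wrong. Open-label and non-blinded appear in a sentence that compares regimens and can be read as describing treatment. This is a condensed article, and slide handling may be set out in the full protocol or a laboratory manual. That stands in part: a reader might infer that biopsies will be read unmasked, and no section says so. What remains is that the label is stated twice, adds non-blinded to open-label and exempts nobody. If masked reading is planned, the published label is misleading and needs the same correction.

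The second reply is that the plan already deals with reader subjectivity for the primary endpoint by choosing computerized image analysis. This also stands in part, and it makes Banff and BPAR the more exposed readings. The Discussion's remark on observer variation should not be pressed further: it concerns comparison across centres, this trial has one centre, and variation between observers is not evidence of a lean towards one arm.

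A reader might also infer that the two biopsies are stained months apart, or that stain thresholds are set by hand. The article says neither. Finally, the false-positive rates are correct arithmetic on an assumed shift. They do not show that such a shift will occur.

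**Conclusion.** The point holds as a design weakness that should be corrected: the trial as labelled leaves room for arm-aware reading of its primary endpoint and of BPAR, and a feasible safeguard is not stated. It is not shown that reading will be unmasked or that results will be biased.

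The illustrated size is modest for a small shift (0.5 point: about 6%) and serious for a larger one (1 point: about 11%; 2 points: about 28%). It rests on SD 5, about 25 evaluable patients per arm, no true effect, and a shift whose size the documents do not give. For Sirius Red it also assumes that some human choice survives the image analysis. The conclusion for Banff and BPAR needs no such assumption, because that grading is visual, but its size cannot be put in figures from the documents.

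**What to change.** Restate the design, in the abstract and in Study design, as open-label treatment with masked outcome assessment. Add to the fibrosis scoring section that the existing reader scores Sirius Red and Banff on slides coded to hide the arm.

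For-cause biopsies are still read at once for patient care, then re-scored on coded slides for the trial's BPAR endpoint. Because this produces two readings, the plan must state which one counts for the endpoint and which one is reported to the DSMB. If masked reading is already in the full protocol, only the published wording needs to change.

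**Cost.** No new patients, visits, biopsies or assessors, and no change to the sample size. The research score arrives later than the clinical reading, and some slides are scored twice.

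**Limit.** Coding addresses reader bias only. The decision to take a for-cause biopsy is still made with the arm known, and that can also affect the BPAR count.

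**Optional.** Staining each patient's two post-transplant biopsies in one batch and coding the echocardiograms are reasonable extras, but not part of the core change.

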#### Inclusion criteria

For entry in the study, the following criteria must be met:Female or male, aged between 18 and 75 years.Subject is willing to participate in the study, must be able to give informed consent and the consent must be obtained prior to any study procedure.Recipients of a first kidney graft from a deceased, living-unrelated or non-HLA identical living related donor > 50 years of age.Panel Reactive Antibodies (PRA) ≤ 10%.Patients must be able to adhere to the study visit schedule and protocol requirements.If female and of child-bearing age, subject must be non-pregnant, non-breastfeeding, and use adequate contraception.

#### Exclusion criteria

Double organ transplant recipient.Biopsy proven acute rejection (according to the Banff criteria) in the first 6 weeks after transplantation.Patients with evidence of active infection or abscesses (with the exception of an uncomplicated urinary tract infection) before MSC infusion.Patients suffering from hepatic failure.Patients suffering from an active autoimmune disease.Patients who have had a previous BM transplant.A psychiatric, addictive or any disorder that compromises ability to give truly informed consent for participation in this study.Use of any investigational drug after transplantation.Documented HIV infection, active hepatitis B, hepatitis C or TB according to current transplantation inclusion criteria. Subjects who currently an active opportunistic infection at the time of MSC infusion (e.g., herpes zoster [shingles], CMV, *Pneumocystis carinii* (PCP), aspergillosis, histoplasmosis, or mycobacteria other than TB, BK) after transplantation. Malignancy (including lymphoproliferative disease) within the past 2-5 years (except for squamous or basal cell carcinoma of the skin that has been treated with no evidence of recurrence) according to current transplantation inclusion criteria. Known recent substance abuse (drug or alcohol). Contraindications to undergo a BM biopsy. Patients who are recipients of ABO incompatible transplants. Cold ischemia time >30 hrs. Patients with severe total hypercholesterolemia (>7.5 mmol/L) or total hypertriglyceridemia (>5.6 mmol/L) (patients on lipid lowering treatment with controlled hyperlipidemia are acceptable).

Thirty five of the patients will be included in the everolimus/MSC group and 35 patients in the everolimus/standard dose tacrolimus group (Figure 1, study scheme). All patients will receive steroids and induction treatment with alemtuzumab at day 0 and day 1 (15 mg subcutaneously). BM will be harvested just prior to the renal transplantation only from patients randomised to the MSC treatment group. MSCs will be cultured in the GMP laboratory, as previously described [34]. Patients will receive 2 doses of a target of 1,5×10^6^ MSCs per/kg body weight (range 1-2×10^6^) at weeks 6 and 7 after transplantation. The dose of tacrolimus will be reduced to 50% at the time of the second MSC infusion and completely withdrawn 1 week later. At that time point the patient will receive 15 mg prednisolon. The expected period of patient accrual is approximately 24 months. All study procedures will take place at the LUMC.

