**Figure 1 Fig1:**
[figure not shown]
**Study scheme.** In total 70 patients will be included in the study, 18–75 years old. Patients will be randomised prior to transplantation. Thirty five of these patients will be included in the Certican®/MSC group and 35 patients in the Certican®/standard dose tacrolimus group. All patients will receive steroids (100 mg at day 1 to 3, 50 mg at day 4, 20 mg at day 5 to 15, 15 mg at day 15 to 21, and 10 mg after day 22) and induction treatment with alemtuzumab at day 0 and 1 (15 mg subcutaneously)*. Certican® dose will be 1.5 mg b.i.d. with trough levels between 3 and 8 ng/ml. Tacrolimus will be started orally 3 h before surgery (initial dose 2x5 mg ). In the first 6 weeks target trough levels are aimed at 10 ng/ml (range 8 to 12 ng/ml) for tacrolimus and thereafter 6–8 ng/ml. In the MSC treated group, BM will be harvested just prior to the renal transplantation and MSCs will be cultured in the GMP laboratory. Patients will receive 2 doses of a target of 1,5x10^6^ autologous BM MSCs per/kg body weight IV (range 1-2x10^6^) 7 days apart, 6 and 7 weeks after transplantation. The dose of tacrolimus will be reduced to 50% at the time of the second MSC infusion and completely withdrawn 1 week later. Patients will receive at that time point 15 mg of prednisolone. In all patients a renal biopsy will be performed at 4 weeks and at 6 months and scored according to the Banff criteria.

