### Isolation of bone marrow and infusion of MSCs

BM will be aspirated from the posterior iliac crest of all patients under general anesthesia during the renal transplantation. A total volume of 100 a 120 ml will be harvested. The processing of the cells will take place at the GMP Stem Cell Laboratory Facility of the LUMC.

In consented patients, a clinical re-evaluation will be undertaken before the planned infusion of MSCs. A target of 1,5×10^6^ MSCs per/kg body weight (range 1-2×10^6^) will be infused within 30 minutes as indicated. Actual doses of MSCs administered will be documented for each patient. Close monitoring of vital signs (temperature, pulse, respiratory rate, blood pressure, and oxygen saturation) will be measured and documented before MSC infusion, every 15 minutes in the first hour and every 30 minutes in the second hour after infusion.

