### Sample size calculation

In our study a sample size of 25 in each group (or 50 in total) will have a 80% power to detect a difference in mean percentages of fibrosis of at least 25% using a two group t-test with a 0.05 two-sided significance level (alpha). In this calculation we used the following assumptions: we expect the control group (no MSC’s) to have a mean percentage of fibrosis of 18% at 6 months [38-43]. We assume that both groups show equal variability in measured fibrosis and that the common standard deviation is 5% [40]. A mean percentage of 14% in MSC group (25% less fibrosis) is considered a clinically relevant difference. We anticipate that 70% of included patients will have valid measurements (withdrawal included). We therefore plan to include 70 patients in total, 35 in the MSC group and 35 in the control group.

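### Exclusion criteria that can only be met after randomisation, two of them tied to an infusion that controls never receive, allow infected patients to be removed from the MSC arm alone

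*Protocol article*

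**What the plan says.** The legend to Figure 1 fixes the order of events: "Patients will be randomised prior to transplantation". Study design agrees, since bone marrow is taken just before surgery and only from patients allocated to MSC. Allocation is therefore known before the graft is in place, and the trial is open-label.

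The Exclusion criteria section is a single list of exclusions from the study. Several entries cannot be assessed before randomisation:

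- "Biopsy proven acute rejection (according to the Banff criteria) in the first 6 weeks after transplantation"
- "Cold ischemia time >30 hrs"
- "Use of any investigational drug after transplantation"
- "Patients with evidence of active infection or abscesses (with the exception of an uncomplicated urinary tract infection) before MSC infusion"
- "Subjects who currently an active opportunistic infection at the time of MSC infusion", with CMV and BK among the examples given.

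The section on isolation of bone marrow and infusion of MSCs adds that "a clinical re-evaluation will be undertaken before the planned infusion of MSCs". The article describes no corresponding eligibility check for controls at that time.

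**The concern.** Randomisation protects a comparison only if later removals do not depend on the arm. Here a patient can meet an exclusion criterion about six weeks after allocation, and for infection the trigger is an event that exists in one arm only. Whoever judges whether an infection is active also knows the allocation.

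Two comparisons are exposed. CMV, BK and other opportunistic infections are endpoints in their own right, and the Abstract's hypothesis is that MSC treatment lowers their incidence. Removing patients already infected at week 6 from the MSC arm alone would favour MSC on that endpoint, with no further assumption about how infection acts on the graft. The primary fibrosis comparison is affected only if infected patients develop more fibrosis than the rest. That is plausible, but the documents do not establish it.

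**Working it through.** **1. Which criteria are one-sided.**

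| Criterion | Can be met before randomisation? | Anchor | Applies equally to both arms as worded? |
|---|---|---|---|
| Rejection in the first 6 weeks | No | Transplantation | Yes |
| Cold ischaemia over 30 h | No | Surgery | Yes |
| Investigational drug after transplantation | No | Transplantation | Yes |
| Active infection or abscess | No, as anchored | MSC infusion | No |
| Active opportunistic infection | No, as anchored | MSC infusion | No |
| Clinical re-evaluation | No | MSC infusion | No |

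All five exclusion criteria act after randomisation. Only the two infection criteria, together with the re-evaluation, are tied to one arm.

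**2. The plan's own figures.** Sample size calculation gives means of 18% and 14% (a difference of 4 points), SD 5, two-sided alpha 0.05, 80% power and 25 per group. The normal approximation gives 25 per group (power 80.7%). The exact t-test gives 25.5, hence 26, with 79.1% power at 25. Inflating for 70% valid measurements gives 50 / 0.70 = 71.4, against 70 stated. The arithmetic is not in dispute; the 4-point difference is used below as the yardstick.

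**3. False difference if infected patients leave the MSC arm only.** Let q be the share removed and D their excess fibrosis at 6 months. With no treatment effect, the control mean contains the term q × D and the MSC mean does not, so the expected false difference is q × D in favour of MSC. Neither q nor D is in the documents; both are assumed. The rejection probability uses SD 5, 25 controls, 25(1 − q) MSC patients and the noncentral t distribution.

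| q | D (points) | q × D (points) | Share of 4 points | Two-sided type I error |
|---|---|---|---|---|
| 5% | 2 | 0.1 | 2.5% | 0.051 |
| 10% | 4 | 0.4 | 10% | 0.058 |
| 20% | 4 | 0.8 | 20% | 0.082 |
| 20% | 8 | 1.6 | 40% | 0.181 |

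The low end is negligible and the high end is not. If the analysis is of change from the 4-week biopsy, as the primary endpoint wording may intend, any excess fibrosis already present at week 4 cancels and D shrinks accordingly.

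**4. Cost of retaining uninfused patients.** Suppose a share q of the MSC arm is not infused and gains nothing. The 4-point effect becomes 4(1 − q): 3.6 points at 10% and 3.2 points at 20%. At 25 per group and SD 5, t-test power falls from 79% to 70% and 60%. Removing the same share instead, with the effect held at 4 points, leaves 25(1 − q) MSC patients and power of 77% and 74%, at the price of the selection described above. Retention also raises the number analysed above what removal would leave, which offsets part of the loss.

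**The case against.** The strongest reply is that the wording is ambiguous. The two infection criteria and the re-evaluation can be read as conditions for giving the infusion, not for staying in the trial. Nothing in the article says that a patient who fails them loses follow-up, the 6-month biopsy or a place in the analysis. The legend to Figure 1 plans the 6-month biopsy for all patients, and Table 1 schedules the week-6 visit and the CMV and BK loads without distinction by arm. Analysis sets are often left to documents not shown here. The routine valganciclovir and cotrimoxazole prophylaxis should also keep some of the listed infections rare.

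Much of this stands. It limits the size of the problem and shows that a symmetric check is feasible. It does not remove the point, because the article places these criteria under exclusion from the study, and that rule as stated permits removal from one arm.

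Three stronger readings are tempting and are not supported:

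- A reader might infer that rejecting patients also leave the MSC arm selectively. The rejection criterion runs from transplantation in both arms, and the 4-week biopsy is taken in all patients.
- A reader might take "We anticipate that 70% of included patients will have valid measurements (withdrawal included") as evidence of selective removal. That figure is an overall allowance covering unusable measurements as well as withdrawals, and it is not linked to the exclusion list.
- A reader might conclude that an infected control is known to stay in. The article does not say so; it only gives no rule that would remove one.

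**Conclusion.** The point holds as an inconsistency between the time of randomisation and the exclusion criteria. Every criterion listed above can remove patients after randomisation. The infection criteria, read literally, can do so in the MSC arm only, in an open-label trial where infection is itself an endpoint.

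The direction for the infection endpoint follows from the wording if infected patients are in fact removed. For fibrosis, both direction and size depend on assumptions: 0.1 to 1.6 points over the ranges shown, or 2.5% to 40% of the planned difference, and less on a change-from-week-4 analysis. The documents do not show that such removal will happen, only that the stated rule allows it.

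**What to change.** Reconcile Exclusion criteria with the time of randomisation:

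1. State that a criterion first met after randomisation does not remove a patient from follow-up or from the primary analysis.
2. Analyse all randomised and transplanted patients in their assigned arm, with the 6-month biopsy already scheduled, whether or not MSCs were infused.
3. If a set of patients eligible at week 6 is wanted, define it by the same check, with the same tests, at the week-6 visit in both arms, and report it as a sensitivity analysis.

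No change to who may be infused is proposed. The cost is amendment wording and an analysis-set definition, since the visit, viral loads and biopsy are already in Table 1. The drawback is dilution by uninfused MSC-arm patients, as quantified above. It grows with their number and should be acknowledged when the sample size is next reviewed.
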